### 2.9 Follow up

Assessment of treatment response will be performed every two cycles for a maximum of eight cycles. The first tumor assessment will be done within 1 weeks before ICI plus chemotherapy initiation and after PDT if PDT is administered in this subject. Reports of adverse events will be obtained during the whole study period through patient interviews or phone contacts. For PDT-treated patients, blood and tumor specimens will be obtained before light illumination on the day of the PDT operation and 48 h after the PDT operation. Diseases examinations and laboratory studies will be repeated at each cycle of treatment and 1 month after the last dose is received.

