### 2.5 Study interventions

Included patients will be divided into the test group and control group. In the test group, patients will receive a PDT operation followed by ICI plus chemotherapy. In the control group, only ICI plus chemotherapy will be performed. 48 h before the PDT procedure, a photosensitizer (hematoporphyrin injection, Hiporfin^®^) will be intravenously injected into the patients in the test group. The dose of photosensitizer is determined based on the weight of patients after carefully evaluating the patient’s kidney and liver function (3–5 mg/kg). Patients with injected photosensitizer will be kept in the dark ward to avoid light exposure until the PDT operation. During the PDT operation, basal anesthesia will be given to the patient first. Then, a gastroscope-based PDT treatment will be administered with a 630 nm laser light delivered by a cylindrical fiber. The cylindrical fiber will be placed near the tumor to ensure complete illumination, and a multi-fractions illumination may be used in some cases (e.g., the tumor is too large to illuminate within one fraction of illumination). The laser light will be generated by the semiconductor laser photodynamic therapy instrument (PDT 630II, Guilin Xingda Photoelectric Medical Equipment Co., Ltd). The parameter of illumination will be set as 800 mW for 15 min with a total energy of 720J. Considering the advanced patients we will include, the patients will receive PDT illumination for four continuous days with the same procedure. After the PDT treatment, patients will be avoided direct light exposure for at least 1 month. In the second week after PDT, patients will receive ICI (Sintilimab or Camrelizumab, 200 mg, day 1, every 3 weeks) plus chemotherapy [SOX (Tegafur gimeracil oteracil potassium capsule twice a day, day 1–14, and oxaliplatin 130 mg/m^2^, day 1, every 3 weeks) or XELOX (capecitabine 1,000 mg/m^2^ twice a day, days 1–14, and oxaliplatin 130 mg/m^2^, day 1, every 3 weeks)]. Tegafur gimeracil oteracil potassium capsule and capecitabine will be orally administered, and others will be intravenously administered. PDT will be only used in the first cycle of treatment for the patients in the test group, which means only ICI plus chemotherapy will continue in the following cycles of treatment. For patients in the control group, the same ICI plus chemotherapy scheme will be given, but no prior PDT operation will be performed in the first treatment cycle.

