### 2.7 Outcomes

The primary outcomes are objective response rate (ORR) and progression-free survival (PFS). The best overall response from ICI plus chemotherapy initiation to disease progression or last follow-up will be used to analyze the ORR. ORR refers to the proportion of patients with complete response (CR) and partial response (PR). PFS is defined as the time from ICI plus chemotherapy initiation to the date of first documented tumor progression or death no matter which happens first. All evaluations of treatment response or progression will be conducted by experienced radiologists according to the RECIST 1.1 criteria (Eisenhauer et al., 1990). The safety will be assessed using the incidence of adverse events defined as any toxicity from intervention initiation to the study end according to the NCI-CTCAE 5.0 criteria (Institute, 2017). For patients who receive PDT treatment, a self-control assessment before and after PDT will be performed, in which the changes in peripheral blood mononuclear cells (PBMCs) and intratumoral gene expression profiles will be evaluated.

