### 2.8 Investigation methods

The tumor will be assessed using contrast-enhanced CT of the abdomen at baseline and each following visit for all included patients. According to the NCI-CTCAE 5.0, any adverse event during the study will be recorded with their types, severity, start and end time, and relatedness to interventions. Blood and tumor tissue specimens before and after PDT will be collected from PDT-treated patients for corresponding tests. After the pre-processing of the blood specimens, PBMC analysis will be performed using flow cytometry to detect the following cells: total T lymphocytes (CD3^+^), cytotoxicity T cells (CD8^+^), CD4^+^ T cells (CD4^+^), and T regulatory cells (Tregs, CD4^+^ CD25^+^ FOXP3^+^). Specimens of tumor tissues will be assessed with an RNA-seq test to investigate the spatiotemporal changes in the expression profile. All patients will receive tumor histological examination [HE stain and immunohistochemistry (IHC)], routine laboratory studies, ECG, chest X scan, ECOG scoring, physical examination, and records of vital signs and concomitant medications. The work timeline and corresponding investigated items are listed in Table 1.

**TABLE 1 T1:** Schedule for the important events in this trial.

Items	Screening phase (within 1 week)	Treatment phase				Follow up phase
		Test group			Control group	
		Cycle 1 (before PDT)	Cycle 1 (after PDT and before ICI plus chemotherapy)	Cycle 1 and beyond (day 1 for ICI plus chemotherapy)	Cycle 1 and beyond (day 1 for ICI plus chemotherapy)	
Informed consent	X					
Inclusion and exclusion criteria	X					
Tumor histological examination	X					
Medical history	X					
Physical examination	X			X	X	X
Vital signs	X			X	X	X
Performance status (ECOG)	X			X	X	X
Concomitant medications	X			X	X	X
Electrocardiogram (ECG)	X					
Chest X scan	X					
Laboratory tests (including blood routine examination, chemistry test, coagulation function, tumor marker, and thyroid function)	X			X	X	X
Pregnancy test (women only)	X			X	X	X
Photosensitizer injection and skin test		X				
Collection and analysis of blood and tumor tissue specimens		X	X			
Tumor assessment by CT	X		X	X (in the cycle 2, 4, 6, and 8)	X (in the cycle 2, 4, 6, and 8)	X
Adverse events assessment		Continuously				X

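### Tumour scans are scheduled by treatment cycle, so PFS is biased toward whichever arm has more cycle delay, if delays differ

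*Protocol article*

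**What the plan says.** - **Scan schedule.** Section 2.9: "Assessment of treatment response will be performed every two cycles for a maximum of eight cycles". The abstract says the same. The CT row of Table 1 (section 2.8) reads "X (in the cycle 2, 4, 6, and 8" for both arms.
- **A second wording.** The text of section 2.8 says "The tumor will be assessed using contrast-enhanced CT of the abdomen at baseline and each following visit for all included patients". This disagrees with section 2.9 on frequency, but the treatment visits in Table 1 are also defined by cycle, so scans follow dosing on either reading.
- **Cycle length.** Section 2.5 gives "ICI (Sintilimab or Camrelizumab, 200 mg, day 1, every 3 weeks", and the chemotherapy is also on a 3-week cycle. The nominal scan interval is therefore 2 × 3 = 6 weeks.
- **PFS.** Section 2.7 starts the clock when ICI plus chemotherapy begins and runs it "to the date of first documented tumor progression or death no matter which happens first". PFS is a primary outcome in both the abstract and section 2.7. Section 2.13 compares it by log-rank test and Cox regression.
- **PDT relative to time zero.** Section 2.5: "PDT will be only used in the first cycle of treatment for the patients in the test group". It comes before ICI plus chemotherapy. On the pre-treatment scan, section 2.9 says "The first tumor assessment will be done within 1 weeks before ICI plus chemotherapy initiation and after PDT if PDT is administered in this subject".
- **Blinding.** Section 2.10 makes the trial open-label.

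**The concern.** Radiological progression is known only from the scan that shows it. When scans follow dosing, each postponed cycle moves all of that patient's later scans, and so the recorded progression date, by the same amount. If both arms are delayed equally, this costs precision but does not bias the comparison. If one arm is delayed more, its progressions are recorded later with no difference in disease course.

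Two features make the log-rank test sensitive to this. It uses the order of event times, so a small systematic lag at each scan wave is enough to place one arm's events behind the other's. Also, the delayed arm's last wave of events can fall after the other arm's last scan, when few or no patients in that arm are still at risk, and those events then hardly count.

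At stake is a primary endpoint in a trial of 30 per arm, in which the staff who set cycle dates know the allocation.

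**Working it through.** The article gives no figure for PFS, scan timing or delays, so there is no figure of the plan to reproduce. The check is a simulation with no true treatment effect.

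**Inputs from the article:** 30 per arm; 3-week cycles; scans at cycles 2, 4, 6 and 8; a visit 1 month after the last dose (section 2.9); PFS clock from the start of ICI plus chemotherapy; two-sided log-rank test at 5%, so 2.5% false positives are expected in favour of each arm.

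**Assumptions:** exponential PFS with a median of 26 or 30 weeks; scans at the end of the named cycle; random one-week delays with probability m/7 per cycle, giving a mean of m days; every event detected at a scan. Deaths are dated exactly in practice, so a share of deaths would dilute the effect.

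**Shift in scan dates.** With a mean delay of d weeks per cycle, the scan at cycle k falls at week k × (3 + d).
- d = 0: weeks 6, 12, 18, 24.
- d = 2/7 (2 days): weeks 6.6, 13.1, 19.7, 26.3, that is 4, 8, 12 and 16 days late.

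**Position of the final scan.** One month is about 4.3 weeks. If the last dose is day 1 of cycle 8, the final visit falls 4.3 − 3 = 1.3 weeks after that cycle ends. If it is the day-14 oral dose, the gap is 4.3 − 1 = 3.3 weeks. The article does not say which, and it matters below.

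**Results** (2,500 trials per setting; hazard ratio from the log-rank score (O − E)/V; below 1 favours the arm with more delay):

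| Setting | Apparent HR | False positives favouring the more delayed arm |
|---|---|---|
| Equal delays | about 1.00 | 2.4–2.8% (test arm) |
| 1 extra day per cycle | 0.92–0.95 | 2.7–4.2% |
| 2 extra days per cycle, final gap 1.3 weeks | 0.86–0.88 | 4.5–5.9% |
| 2 extra days per cycle, final gap 3.3 weeks | 0.91–0.94 | 3.5–4.1% |
| 2 extra days, cycles 1 and 2 only | 0.93–0.98 | 3.1–3.5% |

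The Monte Carlo standard error near 2.5% is √(0.025 × 0.975 / 2,500) = 0.3 percentage points, so the low end of the one-day row cannot be told from no bias.

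**Direction.** With the 2 extra days in the control arm instead, the test-to-control hazard ratio is 1.15–1.16. The sign follows the delay and has nothing to do with PDT as such.

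**A second model.** Fixed delays of 0.25 to 1 week per cycle in one arm, assumed medians of 5 to 9 months and 2,000 trials per setting give hazard ratios of 0.82–0.87 and 5–7% false positives in favour of that arm.

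**Calendar scans.** With scans at fixed weeks from the start of ICI plus chemotherapy and the same imbalance in delay, the hazard ratio returns to 0.99–1.02.

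**The case against.** A reader might infer that PDT will delay cycles and that PFS is therefore biased toward PDT. The article does not support that:

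- It gives no delay rate for either arm, and section 3 expects no significant added safety risk from PDT in theory.
- PDT is given once, before time zero. Slow recovery before the first ICI dose moves the clock and the later scans together. Only delays after that dose can bias PFS.
- Two extra days per cycle, built from one-week delays, means 2/7, or about 29 percentage points, more delayed cycles, sustained over eight cycles after a single PDT course. That is a demanding scenario. Confined to cycles 1 and 2, the effect is small.
- The size also depends on how the final visit is read.

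These points stand, and they limit the finding to a conditional one with no presumed direction. They do not remove it. Safety is itself an outcome of the trial, so the scan schedule should not rely on its turning out equal. The arms do differ in ways that could affect cycle timing: only the test arm has the photosensitizer, anaesthesia, four days of illumination and at least a month of light avoidance, which overlaps the first cycle. The discussion itself concedes a risk of bias from the open-label design.

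It can also be said that scan windows and rules for late cycles belong in the full protocol, which is not shown. Their absence is not the point here. The point is the cycle-based schedule that the article states in three places, and an analysis plan cannot move scan dates afterwards.

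**Conclusion.** The concern holds in conditional form. Scans tied to cycles, with PFS dated at documented progression, leave a primary endpoint open to bias toward the arm with more cycle delay, in either direction. Under the assumptions above, 1 to 2 extra days per cycle gives an apparent hazard ratio of about 0.86 to 0.95 in favour of that arm and about 3 to 6% false positives in its favour, against 2.5%. The range reflects the size of the delay and the timing of the final scan. If the imbalance lasts only two cycles, the hazard ratio is about 0.93 to 0.98, and with equal delays there is no bias. Neither the presence nor the direction of an imbalance can be established from the article. The case for changing the schedule is that the weakness is avoidable at almost no cost before scanning and cannot be fully repaired afterwards.

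**What to change.** In section 2.9, the CT row of Table 1 and the abstract, replace the two-cycle interval with fixed calendar weeks in both arms, for example weeks 6, 12, 18 and 24 within a few days, whatever the cycle delay. Bring the each-visit wording in section 2.8 into line in the same edit.

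Count the weeks from the same origin as the PFS clock. As section 2.7 stands, that is the start of ICI plus chemotherapy. Randomisation should be used only if the PFS origin is moved there too. Mixing the two would create a new bias. With an assumed lead-in of 2.5 weeks for PDT, scans at weeks 6, 12, 18 and 24 from randomisation would fall at weeks 3.5, 9.5, 15.5 and 21.5 of the test arm's PFS clock. In null simulations this gives hazard ratios of 1.03 to 1.26 against PDT, depending on the final-scan gap.

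The cost is wording and one table row, and the number of scheduled scans is unchanged. The small downside is that after a delayed cycle a scan may not fall on a treatment day. No dose or treatment rule is affected.

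### The RECIST reference scan is never named, and the plain reading of sections 2.7 and 2.9 gives a post-PDT baseline in the test arm and an untreated one in controls

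*Protocol article*

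**What the plan says.** Section 2.8 promises a common starting scan: "The tumor will be assessed using contrast-enhanced CT of the abdomen at baseline and each following visit for all included patients". Table 1 marks a CT in the screening column without a split by arm. It adds one CT for the test group only, after PDT and before ICI plus chemotherapy, and then CTs in cycles 2, 4, 6 and 8 for both groups.

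Section 2.9 makes the opening assessment depend on the arm: "The first tumor assessment will be done within 1 weeks before ICI plus chemotherapy initiation and after PDT if PDT is administered".

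Section 2.7 opens the response window at the start of systemic therapy: "The best overall response from ICI plus chemotherapy initiation to disease progression or last follow-up will be used to analyze the ORR". PFS has the same time zero. Section 2.7 invokes RECIST 1.1 but names no reference scan, and no other section does.

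**The concern.** A response rate is a comparison with a reference scan. PDT is part of the strategy being tested, so a reference taken after PDT removes from the comparison whatever PDT did to the tumor up to that point. The control arm has no such reset. Swelling or growth before the reset scan makes a response easier to reach in the test arm, and shrinkage makes it harder. Even without a direct PDT effect on the measured lesions, growth during a lead-in without systemic therapy would be absorbed in one arm only.

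This touches the ORR, which section 2.7 names as a primary outcome (the abstract lists it as secondary) and on which section 2.11 bases the sample size. The trial is open-label. A test-arm patient has two candidate baselines and a control patient has one, so leaving the choice open until results are visible is an avoidable risk.

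**Working it through.** **1. Which scan fits section 2.9?** In controls, Table 1 has no CT between screening and cycle 2. The scan in the week before systemic therapy is therefore the screening CT, and the sections agree.

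In the test arm they do not. Section 2.5 puts the photosensitizer 48 h before PDT, then says "the patients will receive PDT illumination for four continuous days with the same procedure", then "In the second week after PDT, patients will receive ICI". Suppose the screening CT is done as late as the day of the injection. If the second week is counted from the last illumination, the interval from that CT to ICI is at least 2 + 3 + 7 = 12 days. Counted from the first illumination, it is at least 2 + 7 = 9 days. Both exceed the one-week window, and the screening CT is in any case not after PDT. Only the additional post-PDT CT satisfies section 2.9.

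**2. What a shifted reference does.** The documents cite RECIST 1.1 without its thresholds. I assume a 30% fall for partial response and a 20% rise for progression. Let B be the sum of diameters at screening and c its relative change by the post-PDT scan. The documents give no value for c, so it is varied. With the post-PDT scan as reference R = B(1 + c):

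- fall from screening at the partial-response threshold = 1 - 0.7(1 + c)
- change from screening at 20% above the reference = 1.2(1 + c) - 1

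| c | R (B = 100) | Sum at PR | Fall from screening | Sum at R + 20% | Change from screening |
|---|---|---|---|---|---|
| +20% | 120 | 84 | 16% | 144 | +44% |
| +10% | 110 | 77 | 23% | 132 | +32% |
| 0 (as in controls) | 100 | 70 | 30% | 120 | +20% |
| -10% | 90 | 63 | 37% | 108 | +8% |
| -20% | 80 | 56 | 44% | 96 | -4% |

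If the illuminated lesion contributes only a fraction f of the sum, c shrinks in proportion. With f = 0.5 (assumed) and a 20% change in that lesion, c is ±10%, and the range narrows from 16%-44% to 23%-37%.

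**3. Progression is less clear-cut.** Suppose progression is judged from the smallest sum on study (an assumption). After 20% shrinkage, the post-PDT sum of 80 is the minimum under either baseline, and the threshold is 80 × 1.2 = 96 in both cases. After 20% growth, a screening baseline puts the threshold at 120. The post-PDT scan itself then reaches it, before the PFS clock has started.

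**4. Sensitivity of the ORR comparison.** The planned size can be reproduced. For 50% against 85%, two-sided 5%, 80% power, unpooled variance: n = (1.960 + 0.842)² × (0.25 + 0.1275) / 0.35² = 24.19, so 25 per group, and 25 × 1.2 = 30. The baseline question does not alter this figure.

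With 30 per group and a control ORR of 50%, power (pooled normal approximation) is 84% at an observed-scale test ORR of 85%, 69% at 80%, 52% at 75% and 35% at 70%. In the other direction, if the true ORR is 50% in both arms but the shifted reference raises the measured test-arm rate to 60%, the chance of a significant result favoring PDT is about 12%, against a nominal 2.5%. How far a given c moves the ORR cannot be derived from the documents.

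**The case against.** The strongest reply is that the protocol does not call the post-PDT scan the baseline. Section 2.9 fixes the timing of an assessment. Section 2.7 fixes the period in which responses count. The word baseline appears in section 2.8, applied to all patients, beside a screening CT common to both arms. A reader might infer that the plan has definitely adopted different RECIST baselines by arm. The text does not go that far, and this part of the reply stands: the reference is unnamed and the passages conflict. It does not dispose of the point, because section 2.9 states an arm-dependent rule that the screening CT cannot meet in the test arm.

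A reader might also infer that the bias is irrecoverable or that it favors PDT. Neither is supported. The screening CT exists in every patient and could be re-read, and the direction depends on an unknown c.

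It can fairly be added that section 1 describes PDT as a local therapy of limited depth, and that section 2.3 requires only one measurable lesion, which need not be the illuminated one. That dilutes direct swelling or shrinkage, but not growth during the lead-in. Finally, aligning scans to the start of ICI has some logic if PDT is seen purely as an adjunct. But section 2.1 sets out to evaluate the efficacy of the combination, to which PDT's own effect belongs.

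**Conclusion.** The point holds as an unnamed and internally contradictory RECIST reference whose plain reading differs by arm. It is more than detail left to a fuller document, because the article itself states the arm-dependent timing. The size is illustrative only: under an assumed change of +20% to -20% before the post-PDT scan, and a 30% threshold for partial response, the response criterion in the test arm corresponds to a 16% to 44% fall from the pre-treatment scan, against 30% in controls. The effect on response is firmer than the effect on progression, which depends on how the nadir is defined. It should be settled before outcome data are seen. Once results are known, even a recoverable choice between two baselines is no longer prespecified.

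**What to change.** State in section 2.7 that the pre-treatment screening CT is the RECIST 1.1 baseline for target-lesion selection and for all percentage changes in both arms. Keep the post-PDT CT as a descriptive assessment and as the baseline of a sensitivity analysis.

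Naming the baseline is not enough by itself. Also state whether the post-PDT CT may set the nadir, and whether growth on it counts as a progression event. If it does, the ORR and PFS windows in section 2.7 must open early enough to contain it, for instance at randomization in both arms. Then reword section 2.9 so that the post-PDT CT is no longer called the first assessment, and bring sections 2.7, 2.8 (with Table 1) and 2.9 into agreement.

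The cost is wording and one decision on time zero. Both CTs are already scheduled, so no scan is added. The small downside is an older baseline relative to ICI start in the test arm, by at least 9 to 12 days on the timings above.

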### 2.10 Allocation and blinding

Patients will be randomly allocated into the test group and control group at a ratio of 1:1. An independent researcher who will not take roles in patient recruitment will generate a random sequence table using the R software, and the paper strips with allocation results will be kept in a non-transparent envelope. Once the patient is recruited, the doctor will assign the interventions according to his allocated group. As it is difficult and almost impossible to set blind for PDT treatment, this trial is set as open-label.

### 2.11 Sample size estimation

We calculate the sample size based on the ORR. According to the published report, 48.6% of patients receiving ICI plus chemotherapy had an objective response (Shitara et al., 2020). Thus, we expected the ORR to be 50% in our control group. For the patients receiving PDT in combination with ICI plus chemotherapy, we assume that 85% of patients will obtain an objective response based on the experience from our center. Based on these expected proportions, we use a two-sided type I error of 5% with a power of 80% to determine the required lowest sample size. It is supposed that approximately 20% of patients may drop out of the trial. Considering all of these, a total of 60 patients (30 per group) are planned to enroll.

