### 2.13 Data analysis

All statistical analyses will be performed using the R software (version 4.0.2). The intention-to-treat and per-protocol approaches will be used for the analysis of the primary outcomes. The as-treated analysis will be used for safety analysis. Continuous data will be presented as mean with standard deviation or median with interquartile range. Categorical data will be presented as numbers with percentages. Student’s t-test or Mann-Whitney *U*-test will be used for the comparison of continuous data, while chi-squared test or Fisher’s test will be used for categorical data. For patients in the test group, the paired *t*-test or Wilcoxon signed-rank test will be used to analyze the difference in PBMC data before and after PDT treatment. The analysis of the gene expression profile will follow the standard procedure for transcriptomic analysis, and a protocol will be developed once the specimens are collected. The survival plot will be drawn for PFS using the Kaplan-Meier method. Log-rank test will be used to compare the difference between the two groups, and Cox regression analysis will be performed to estimate the hazard ratio with 95% CI. All statistical tests will be two-sided, and a significant level will be set at 5%.

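### With 24 evaluable patients per arm after the plan's own 20% drop-out, neither the chi-squared nor the Fisher test reaches the stated 80% power for ORR

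*Protocol article*

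**What the plan says.** Section 2.11 of the protocol article bases the sample size on response: "We calculate the sample size based on the ORR". The control assumption is "Thus, we expected the ORR to be 50% in our control group", and for the test group "we assume that 85% of patients will obtain an objective response based on the experience from our center". The error rates are given as "we use a two-sided type I error of 5% with a power of 80% to determine the required lowest sample size". On losses it says "It is supposed that approximately 20% of patients may drop out of the trial", and the result is "a total of 60 patients (30 per group) are planned to enroll". Allocation is equal (section 2.10). The section gives no formula, no number before drop-out and no method of inflation.

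Section 2.13 supplies the test in general terms: "chi-squared test or Fisher’s test will be used for categorical data". It plans both intention-to-treat and per-protocol analyses of the primary outcomes, and section 2.7 lists ORR among these.

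**The concern.** The 80% is the only power figure in the article. It is stated after a 20% drop-out allowance, so a reader will take it as the power that remains once those losses have occurred. Whether that is true depends on the test used, and at this size the two named tests differ by about 10 points of power. If the real figure is nearer 67% than 80%, a non-significant ORR result would be read as stronger evidence against benefit than it is. The assumed 35-point difference is also large, so there is little margin if the true effect is smaller. Leaving the ORR test open in an open-label trial also leaves a choice that could be made after the data are seen.

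**Working it through.** **Inputs.** From section 2.11: control ORR 0.50, test ORR 0.85, two-sided 5%, power 80%, drop-out 20%, 30 per group. From section 2.10: 1:1 allocation. From section 2.13: chi-squared or Fisher's test.

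**1. Can the plan's 30 be reproduced?** Difference d = 0.35, so d² = 0.1225. Sum of variances = 0.50×0.50 + 0.85×0.15 = 0.25 + 0.1275 = 0.3775.

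- Unpooled normal formula: n = (1.96 + 0.8416)² × 0.3775 / 0.1225 = 24.19 per arm. Allowing for drop-out, 24.19/0.8 = 30.2. This matches 30 to the nearest patient; strict rounding up gives 31.
- Pooled formula, which corresponds to the usual chi-squared test: mean rate 0.675, n = [1.96×√(2×0.675×0.325) + 0.8416×√0.3775]² / 0.1225 = 26.9, so 27 per arm, and 27/0.8 = 33.75, so 34.
- Arcsine formula: 26.1, so 27 per arm, and again 34.
- Pooled with continuity correction: 32.4, so 33 per arm, and 33/0.8 = 41.25, so 42.

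Of these four, only the unpooled approximation with division by 0.8 lands on the plan's figure.

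**2. Evaluable number.** 30 × 0.8 = 24 per arm.

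**3. Power at 24 per arm.** The unpooled approximation gives Φ(0.35/√(0.3775/24) − 1.96) = Φ(0.83) = 79.7%, in effect the stated 80%. The pooled approximation gives 75.1%. Exact power was found by enumerating every pair of binomial counts and adding the probabilities of the pairs with p ≤ 0.05.

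| Situation | Chi-squared, uncorrected | Chi-squared, continuity-corrected | Fisher |
|---|---|---|---|
| 24 per arm, 50% vs 85% | 76.7% | 64.0% | 66.8% |
| 30 per arm, no loss, 50% vs 85% | 84.7% | 77.7% | 77.7% |
| 30 per arm, all drop-outs counted as non-responders, 40% vs 68% | 60.1% | 49.5% | 49.5% |

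The last row is an assumption: the article does not say how drop-outs enter the intention-to-treat ORR. Its rates are 0.8×50% = 40% and 0.8×85% = 68%.

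**4. Evaluable number needed for 80% exact power.** Uncorrected chi-squared needs 26 per arm (80.9%), and 26/0.8 = 32.5, so 33 enrolled per arm. Fisher needs 32 per arm (81.5%), and 32/0.8 = 40 enrolled per arm.

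**5. Type I error of the uncorrected chi-squared test at 24 per arm.** By the same enumeration it is 5.9% at a common rate of 50% and 5.5% at 60%. Part of its power advantage over Fisher comes from this.

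**The case against.** A planning formula often differs by a few points from the exact power of the final test, and against uncorrected chi-squared the gap here is 80 − 76.7 = 3.3 points. That is fair, and it is why this is not a fatal flaw.

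The test sentence in section 2.13 is generic and covers all categorical data, so Fisher may not be meant for ORR. The mean expected number of non-responders is 24 × 0.325 = 7.8 per arm (9.75 at 30), and on the usual expected-count convention chi-squared would apply. This makes the 13-point Fisher shortfall less likely. It does not remove it, because the sentence leaves the choice open.

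The shortfall also depends on drop-outs being unevaluable or counted as failures. If all 30 per arm are analysed at the assumed rates, uncorrected chi-squared exceeds 80%. That stands.

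A reader might infer that the authors multiplied by 1.2 instead of dividing by 0.8, since 25 × 1.2 = 30. The documents do not support this. Section 2.11 shows neither 25 nor 1.2, and the unpooled formula with correct division also gives about 30. A reader might likewise quote 60% as the intention-to-treat power. That holds only if every drop-out counts as a non-responder, which the article does not say. Section 2.7 uses best overall response up to progression or last follow-up, so a patient who leaves after responding could still count as a responder.

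**Conclusion.** The point holds on the condition that drop-outs are not evaluable. With 24 per arm, exact power is 76.7% for uncorrected chi-squared, 66.8% for Fisher and 64.0% with continuity correction, all below the stated 80%. The likely source is an unpooled normal approximation that is more favourable than the tests named in section 2.13; a faulty drop-out inflation is not shown. Fisher falls short even with no loss (77.7%). Uncorrected chi-squared does not (84.7%). The size is therefore modest for one named test and material for the other, and the open choice between them is what makes the stated figure unreliable. This should be fixed. It does not require more patients, and it does not show that the trial was mis-sized by a gross error.

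**What to change.** Keep 60 patients.

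- **Section 2.11:** state the formula and the evaluable number per arm (24). Restate power at that number as about 77% for uncorrected chi-squared or about 67% for Fisher, whichever is chosen. Give any intention-to-treat figure as conditional: about 60% (chi-squared) or 50% (Fisher) if all drop-outs count as non-responders, up to about 85% or 78% if all 30 per arm are analysed at the assumed rates.
- **Section 2.13:** name one test for ORR in advance. If it is the uncorrected Pearson chi-squared test, note that its actual type I error at 24 per arm can slightly exceed 5% (about 5.9% at a common rate of 50%). If it is Fisher's test, type I error is held but about 10 points of power are given up.

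The cost is a rewording of section 2.11, one line in section 2.13 and a less favourable stated power. If 80% after drop-out were to be kept as a firm target, exact power would call for 33 per arm (66 in total) with uncorrected chi-squared or 40 per arm (80 in total) with Fisher. Restating the power avoids that.
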